### 2.8. Outcomes

Assessments will be conducted at four time points: pre-treatment (A1), immediately post-treatment (A2), 24 h post-treatment (A3), and 7 days post-treatment (A4). All assessments will be conducted by an assessor blinded to group allocation and will be performed in the same clinical setting at Clínica CEMTRO (Madrid, Spain), under standardized conditions. The order of outcome assessment will be identical whenever applicable. All outcomes will be assessed according to the schedule presented in Table 2.

Baseline descriptive variables will include sex, age, body mass, height, BMI, limb dominance, operated limb, graft type (hamstring tendon autografts, bone–patellar tendon–bone autografts, quadriceps tendon autografts or allografts), associated lateral extra-articular tenodesis, and meniscal procedures (none, repair, debridement, rasping, partial meniscectomy). Surgery-related sensory disturbances (none, anesthesia, hypoesthesia, hyperesthesia, paresthesia) will also be recorded.

#### 2.8.1. Primary Outcome

Quadriceps maximal voluntary isometric contraction (QMVIC) of the operated limb will be measured using a calibrated hand-held dynamometer (Lafayette Manual Muscle Tester, Lafayette Instruments, Lafayette, IN, USA), which has demonstrated excellent intra-rater reliability [ICC = 0.98; 95% CI, 0.98–0.99] [74]. All measurements will be performed by an assessor experienced in hand-held dynamometry in previous research studies.

Participants will be seated with an upright trunk, 90° hip flexion, and 75° knee flexion [75,76]—a position associated with minimal stress on the ACL graft [77]. Thigh stabilization will be applied to prevent compensatory movements, and participants will be instructed to hold the edge of the treatment table if needed [75,78]. To ensure measurement validity, knee angle will be set using a 360° universal manual goniometer prior to each QMVIC assessment, following the guidelines of Norkin [79]. The dynamometer will be aligned with the lateral femoral condyle, and resistance will be applied to the anterior tibia 2 cm proximal to the malleoli [41,80].

Three maximal contractions of 5 s each will be performed, with 60 s of rest between trials. Standardized verbal encouragement will be provided during each contraction. The highest absolute force value (N) will be recorded [75,76,78,81]. Torque values will not be normalized to body mass or lever arm.

#### 2.8.2. Secondary Outcomes

Secondary outcomes will include pain intensity, pressure pain threshold (PPT), knee range of motion (ROM), thigh muscle perimeter, intra-articular knee effusion, extra-articular knee swelling, and self-reported function and knee-related quality of life.

Pain will be measured using the numerical rating scale (NRS) [82], PPT will be measured at six predefined anatomical points using an analog pressure algometer [83] and ROM will be measured with a universal goniometer [33,79]. Thigh perimeter and knee effusion will be measured with a flexible non-elastic measuring tape [84]. Knee swelling will be assessed clinically [84]. Self-reported function knee-related quality of life will be evaluated using the Lysholm Knee Score [85] and ACL-QoL-Sp [86].

**Pain Intensity**

Pain intensity will be assessed using the NRS, ranging from 0 (no pain) to 10 (maximum imaginable pain), given the general consensus that it provides greater validity compared with visual analog scales and facial or verbal pain rating scales [63].

**Pressure Pain Threshold**

Pressure pain threshold will be measured using an analog pressure algometer (FPK20, Wagner Instruments, Greenwich, CT, USA), consisting of a manometer connected to a 1 cm^2^ rubber probe, with values expressed in kg/cm^2^ (0–10 kg/cm^2^). Pressure will be applied perpendicularly at a constant rate of approximately 1 kg/s until the participant reported the first sensation of pain. At that point, pressure application will be discontinued and the corresponding measurement value recorded [87].

All measurements will be performed by an assessor with previous experience in pressure algometry assessments in prior research studies. Prior to the assessment, participants completed two familiarization trials on the hand. Three measurements will be collected at each anatomical site, with a 30 s interval between trials to prevent temporal summation. The mean of the three values will be used for statistical analysis. If a difference greater than 1 kg/cm^2^ was observed between two consecutive measurements at the same site, the highest value was discarded and an additional measurement was performed [87].

Measurements will be obtained at 5 predefined anatomical points of the operated limb [64], assessed in the same order at each evaluation: vastus lateralis (10 cm lateral to the midpoint of the superior patellar border), quadriceps tendon (3 cm proximal to the superior patellar border), vastus medialis (3 cm medial to the midpoint of the superior patellar border), patellar tendon (midpoint between the inferior patellar pole and the tibial tuberosity), pes anserinus (3 cm medial to the tibial tuberosity), in addition to the ipsilateral lateral humeral epicondyle. The algometer will be the only point of contact with the participant to avoid sensory interference [88].

**Knee Range of Motion**

Active and passive knee flexion and extension ROM will be measured using a 360° universal manual goniometer. The fulcrum will be positioned over the lateral femoral condyle, the proximal arm aligned with the lateral midline of the femur toward the greater trochanter, and the distal arm aligned with the lateral midline of the fibula toward the lateral malleolus [79].

Special care will be taken to avoid eliciting excessive pain during ROM assessment, as this could negatively impact the participant and potentially influence subsequent measurements [33].

**Thigh Muscle Perimeter**

Thigh muscle perimeter will be measured 10 cm proximal to the superior border of the patella using a flexible non-elastic measuring tape [84]. The corresponding measurement will also be recorded on the contralateral limb.

**Intra-Articular Knee Effusion**

Intra-articular knee effusion will be assessed on the basis of bulge and dancing patella signs and reported as to a four-grade scale: 0 (no effusion), 1 (<25 cm^3^, palpable by smoothing out the joint capsule), 2 (25–60 cm^3^, visible effusion), and 3 (>60 cm^3^, tight capsule) [84].

**Extra-Articular Knee Swelling**

Extra-articular knee swelling will be assessed by measuring the knee perimeter from the center of the patella using a flexible non-elastic measuring tape [84]. The corresponding measurement will also be recorded on the contralateral limb.

**Self-reported Function and Quality of Life**

Self-reported function and knee-related quality of life will be evaluated using the Lysholm Knee Scoring Scale [85] and the Spanish version of the Anterior Cruciate Ligament-Quality of Life questionnaire (ACL-QoL-Sp) [86], respectively. Both questionnaires will be administered only at baseline (A1) and at the final follow-up (A4).

The Lysholm Knee Scoring Scale [85] is the most widely used instrument for self-reported functional evaluation following ACLR and assesses limping, use of walking aids, locking, instability, pain, swelling, stair climbing ability, and squatting or crouching ability during activities of daily living. With a maximum possible score of 100 points, scores are classified as: (1) Poor: <65; (2) Fair: 65–83; (3) Good: 84–94; and (4) Excellent: >95.

The study design and experimental protocol timeline are summarized in Figure 2.

### 2.9. Statistical Methods

All statistical analyses will be performed using SPSS statistical software for Windows (version 27.0; SPSS Inc., Chicago, IL, USA). The primary analysis will be conducted according to an intention-to-treat approach, using linear mixed-effects models, which accommodate repeated measures and handle missing data under the missing-at-random assumption.

A complementary per-protocol analysis will be conducted as a sensitivity analysis, including only participants who complete the assigned intervention and all scheduled assessments according to predefined criteria. This dual approach allows evaluation of the robustness of the primary findings.

Data normality will be assessed using the Shapiro–Wilk test. Descriptive statistics will be calculated for baseline characteristics, reporting means and standard deviations for normally distributed variables, and medians with interquartile ranges for non-normally distributed variables.

To evaluate intervention effects over time, repeated-measures analysis of variance (ANOVA) will be applied to outcomes meeting normality assumptions. The within-subject factor will be time (pre-treatment, immediate post-treatment, 24 h post-treatment, and 7 days post-treatment), and the between-subject factor will be group (control: CRP only; TENS: CRP plus a high-frequency TENS session; PENS: CRP plus a LTP PENS session). Bonferroni correction will be used for post hoc comparisons. Sphericity assumptions will be assessed, and Greenhouse–Geisser corrections will be applied as appropriate.

To provide a more flexible and robust analysis of repeated measures, linear mixed-effects models will additionally be applied. These models will include the fixed effects of group, time, and the group × time interaction. They allow inclusion of all available data and appropriately handle missing observations under the missing-at-random assumption without requiring complete cases or sphericity.

Exploratory multivariable analyses will be performed to investigate associations between clinical outcomes and sociodemographic and surgical-related variables, focusing on relationships with surgical procedures. Potential confounding effects of graft type and concomitant procedures on early quadriceps outcomes will not be formally tested, and any subgroup analyses will be limited to descriptive reporting.

A two-sided significance level of α = 0.05 will be adopted, and results will be reported with 95% confidence intervals.

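### The mixed model is named as primary for QMVIC but then listed as an addition to a repeated-measures ANOVA of no stated rank, and no visit or test is named as decisive

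*Protocol article*

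**What the plan says.** Section 2.9 gives the mixed model its rank in the first paragraph: "The primary analysis will be conducted according to an intention-to-treat approach, using linear mixed-effects models, which accommodate repeated measures". The same paragraph relies on the missing-at-random assumption for missing data.

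Later in the section a different method is given the job of testing the treatments: "To evaluate intervention effects over time, repeated-measures analysis of variance (ANOVA) will be applied to outcomes meeting normality assumptions". The only normality criterion named is Shapiro–Wilk: "Data normality will be assessed using the Shapiro–Wilk test". Bonferroni correction for post hoc comparisons appears in the ANOVA paragraph, without a list of the comparisons it covers.

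The next paragraph brings the mixed model back as a supplement: "To provide a more flexible and robust analysis of repeated measures, linear mixed-effects models will additionally be applied". Its terms are then given: "These models will include the fixed effects of group, time, and the group × time interaction".

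Three other places bear on the point:
- The Introduction states the primary objective as adding TENS or PENS to rehabilitation, compared with rehabilitation alone.
- Section 2.8 and Table 2 schedule QMVIC at baseline (A1), immediately after treatment (A2), at 24 h (A3) and at 7 days (A4).
- Section 2.3 sizes the trial for a repeated-measures ANOVA with three groups. It does not say which effect is tested or how many measurements are assumed.

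**The concern.** An analysis cannot be both the primary one and an addition to another. With a single primary outcome, readers need to know in advance which result decides. Here a mixed-model result and an ANOVA result for QMVIC could both be presented as the answer, and they need not rest on the same patients.

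The second gap is the decisive test. The objective calls for two comparisons with control, but the models are described by group, time and their interaction. The interaction has (3 − 1) × (4 − 1) = 6 degrees of freedom and answers a broader question than the objective. Three post-treatment visits are available and none is named. If these choices are made after the data are seen, the error rate of the primary claim is no longer fixed by the plan.

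**Working it through.** **1. Does the sample-size section identify the decisive test?** Inputs from Section 2.3: three groups, f = 0.25, α = 0.05, correlation 0.5, ε = 1, N = 45, power 80%. Four measurements are assumed, from Section 2.8.
- Group × time interaction: λ = f²·N·m/(1 − ρ) = 0.0625 × 45 × 4 / 0.5 = 22.5, with 6 and 126 df. Power is 0.955. For 80% power N = 30 is enough (λ = 15, power 0.809).
- Between-group effect: λ = f²·N·m/(1 + (m − 1)ρ) = 0.0625 × 45 × 4 / 2.5 = 4.5. Power is 0.433, and 80% needs N = 102.
- With two or three measurements the interaction needs 42 or 36. The time effect needs 24 to 36 over two to four measurements.

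None of these gives 45 at 80% power, so the decisive effect cannot be inferred from the sample size.

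**2. Do the two analyses use the same patients?** The mixed model is described as using all available data without needing complete cases. A repeated-measures ANOVA needs every visit. If the 20% dropout of Section 2.3 shows up as incomplete follow-up, it keeps 54 × 0.80 = 43.2, about 43 patients. That is close to the per-protocol set, which Section 2.9 also limits to patients with all assessments.

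**3. What error rate do the open choices allow?** Null simulation with 18 per arm, four visits, compound symmetry with correlation 0.5 or 0.7, and t-tests on change from baseline. Under compound symmetry two change scores correlate (1 − ρ)/(2(1 − ρ)) = 0.5 whatever ρ is, so both settings give nearly the same result.

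| Reading of the plan | Familywise error, global null |
|---|---|
| Two control contrasts × three visits, unadjusted, no omnibus test | about 22% |
| Bonferroni over three pairs within each visit, no omnibus test | about 11% |
| Two control contrasts × three visits, only after a significant interaction | 4.1–4.5% |
| Bonferroni over three pairs per visit, only after a significant interaction | 3.5–3.9% |
| Bonferroni over all 3 × 3 = 9 contrasts, no omnibus test | 4.0–4.4% |

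For comparison, six independent tests would give 1 − 0.95⁶ = 26.5%. If the change scores correlate at 0.7 instead of 0.5, the first two rows fall to about 19% and 10%. The 11% row counts a false TENS–PENS difference as an error too, so the rate for the two control contrasts alone is lower.

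**4. What does the choice cost in power?** Noncentral t with 15 per arm (45/3), pooled df 45 − 3 = 42, noncentrality d·√(15/2), 80% power, and d in SDs of change from baseline:
- two contrasts at one visit, α = 0.05/2 = 0.025: d = 1.16
- nine contrasts, α = 0.05/9 = 0.0056: d = 1.38

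Both use change scores, so the gap of 0.22 is due to multiplicity alone.

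**The case against.** The strongest reply is that the plan does name its primary analysis. Only the mixed model carries that label, and the ANOVA could be read as supportive. The comparator is also fixed by the Introduction, and Bonferroni correction is stated. Post hoc comparisons usually follow a significant omnibus test, and on that reading familywise error under the global null stays near 4%. The exact contrasts and correction family are often left to the analysis plan.

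Much of this stands. A reader might infer that the plan declares two primary analyses, that the Shapiro–Wilk test decides whether the primary analysis runs, or that the true error rate is 22%. The text supports none of these. The ANOVA is never called primary. The normality condition and the complete-case loss apply to the ANOVA only. The 22% needs both no correction and no omnibus test, while the plan does state a correction.

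The reply does not remove the conflict. The ANOVA is given the task of evaluating intervention effects and the sample size was built on it, while the supposedly primary model is introduced as an extra. That is a contradiction in printed text. The omnibus-first order is a convention that the article does not state, and its 4% holds only when neither treatment has any effect. If one treatment works, the gate may open and no longer protect the other comparison.

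**Conclusion.** The point holds as an inconsistency about the single primary outcome. The mixed model has two incompatible roles, the ANOVA has no rank, and neither a decisive visit nor a decisive test is named.

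The size depends on how the gaps are filled: about 4% familywise error on the favourable readings, 11% with correction only within visits, and 22% with none. These figures assume the global null, compound symmetry and 18 per arm. It would be wrong to say that the plan's error rate is above 5%; the plan does not fix it. The loss from 54 to about 43 patients assumes the full 20% dropout and affects only the ANOVA.

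The point concerns QMVIC alone. The method for the ordinal effusion grade is a separate secondary-outcome matter and adds nothing to it.

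**What to change.** Amend Section 2.9 before unblinding:

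1. State that the mixed model on all randomised patients is the sole primary analysis of QMVIC, whatever the normality test shows.
2. Label the repeated-measures ANOVA supportive, or drop it, and reword the sentence that introduces the mixed model as an addition.
3. Name one post-treatment visit as primary. The investigators should choose it on scientific grounds.
4. At that visit test TENS versus control and PENS versus control from the mixed model, with familywise error held at 0.05, for example by Holm or Dunnett.
5. Make the other visits and TENS versus PENS secondary, and state which comparisons any Bonferroni correction covers.

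The cost is wording only, with no change to patients, visits or measurements. What is given up is the option of a primary claim at the other two post-treatment visits.

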### 2.3. Sample Size Calculation

Sample size was calculated using G*Power software (version 3.1) [52] for a repeated-measures analysis of variance with three groups. Assuming a medium effect size (f = 0.25), a power of 80% (β = 0.20), and a two-sided significance level of α = 0.05, a total sample size of 45 participants was required. The calculation was based on a correlation among repeated measures of 0.5 and a nonsphericity correction factor (ε) of 1. To account for an anticipated dropout rate of 20%, a total of 54 participants will be recruited, with 18 allocated to each group (control, TENS, and PENS).

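### The primary mixed model treats pre-randomisation QMVIC as a level of time instead of adjusting for it, an avoidable loss of precision (25% of variance at correlation 0.5, 5% at 0.9)

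*Protocol article*

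**What the plan says.** Section 2.9 names linear mixed-effects models, by intention to treat, as the primary analysis. Their fixed part is given in one sentence: "These models will include the fixed effects of group, time, and the group × time interaction". For the repeated-measures ANOVA in the same section, the time factor is spelled out: "The within-subject factor will be time (pre-treatment, immediate post-treatment, 24 h post-treatment, and 7 days post-treatment". The mixed model is then presented as a more flexible analysis of the same repeated measures, so the natural reading is that it uses the same four levels, although this is not said. Neither a baseline covariate nor a common baseline mean across arms is mentioned. The section does not say whether the group main effect, the interaction or a contrast at a named visit decides the trial.

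Section 2.5 has the envelopes opened only after the baseline assessment. Section 2.5 also rules out stratification by graft type or concomitant procedure. Section 2.8.1 defines the outcome as the highest absolute force in newtons and adds: "Torque values will not be normalized to body mass or lever arm". Section 2.3 gives the planning correlation: "The calculation was based on a correlation among repeated measures of 0.5 and a nonsphericity correction factor (ε) of 1".

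**The concern.** A1 cannot carry a treatment effect, because it precedes allocation. A model with group, time and their interaction over four visits nevertheless estimates a separate A1 mean for each arm. A between-arm contrast taken from it is then either a difference in change from A1 or a difference in raw post values. Neither makes the best use of A1 as a predictor of the later measurement.

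The outcome is unnormalised force in a sample that varies in sex and graft type, with 18 per arm and no stratification. Chance differences at baseline are therefore quite possible, and A1 QMVIC is the obvious variable to absorb them. What is at stake is the width of the intervals on the primary comparisons in a small trial, not the validity of those comparisons.

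**Working it through.** **Inputs.** Correlation 0.5, 45 evaluable (15 per arm), 54 recruited (18 per arm), two-sided α 0.05 (section 2.3); four visits and the fixed effects (section 2.9). Added assumptions: equal variance σ² and the same correlation ρ between all visits.

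**The plan's own figure.** The plan states no precision for any contrast. Its N of 45 is not reproduced from the stated inputs: under G*Power conventions a four-level interaction needs 30 (power at 45 is 95.6%) and a two-level interaction needs 42. That is a separate matter. Only ρ = 0.5 is borrowed here.

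**Single post visit, variance per participant in units of σ².**
- Raw post value: 1
- Change from A1: 2(1 − ρ)
- Adjusted for A1: 1 − ρ²

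Adjusted over change is (1 − ρ²)/[2(1 − ρ)] = (1 + ρ)/2, so the avoidable share is (1 − ρ)/2. Against raw post values the avoidable share is ρ².

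| ρ | Change | Adjusted | Avoidable vs change | Avoidable vs raw post |
|---|---|---|---|---|
| 0.5 | 1.00 | 0.75 | 25% | 25% |
| 0.7 | 0.60 | 0.51 | 15% | 49% |
| 0.8 | 0.40 | 0.36 | 10% | 64% |
| 0.9 | 0.20 | 0.19 | 5% | 81% |

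At ρ = 0.5 the standard error falls by 1 − √0.75 = 13.4%, and 18 adjusted participants per arm are worth 18/0.75 = 24 unadjusted. A simulation of 20,000 trials with 18 per arm gave variances of 0.0859 adjusted and 0.1119 for change, a ratio of 0.767. The small excess over 0.75 reflects the cost of estimating the baseline slope.

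**Mean of the three post visits.** Change: (1 + 2ρ)/3 + 1 − 2ρ. Adjusted: (1 + 2ρ)/3 − ρ². At ρ = 0.5 these are 0.667 and 0.417, ratio 0.625 (37.5% avoidable). At ρ = 0.9 they are 0.133 and 0.123, ratio 0.925 (7.5%).

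**Group main effect over four visits.** A constant post-treatment effect δ is averaged with a zero at A1: (0 + δ + δ + δ)/4 = 0.75δ. Simulation gave 0.602 for a true 0.80. The change contrast gave 0.800 for the same truth, so it is not diluted.

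**Illustrative power, ρ = 0.5, 18 per arm, two-sided 0.05, one post visit.** The effect sizes are assumptions. For 0.5 SD, power rises from 31% to 40%; for 0.8 SD, from 65% to 78%.

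**Illustrative detectable difference, 80% power.** This assumes α = 0.025 (0.05 split over two active-versus-control comparisons) and 15 per arm. The protocol fixes neither for this contrast. Unadjusted and adjusted values are 1.16 and 1.01 SD at ρ = 0.5, 0.73 and 0.70 SD at 0.8, and 0.52 and 0.51 SD at 0.9.

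**Baseline imbalance.** With 18 per arm, the simulated chance that some pair of arms differs at A1 by more than 0.5 SD is 0.29.

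**The case against.** The strongest reply is that this is a preference about efficiency, and a modest one. Under randomisation the planned group × time contrasts are unbiased with valid type I error. Change contrasts already subtract baseline, so chance imbalance leaves only a regression-to-the-mean component. In 71% of trials no pair of arms would differ by more than 0.5 SD. All of that stands.

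The size of the gain is also open to challenge. The 0.5 is a sample-size input, not an estimate for QMVIC. Unnormalised force in a mixed sample, retested in the same limb within seven days, may well correlate more strongly, and the gain over change scores then falls to 10% or 5%. This stands too, and it is why a range is given. The intra-rater ICC of 0.98 in section 2.8.1 does not settle it: repeatability of the instrument is not the correlation across treatment and a week. A higher correlation also makes raw post comparisons worse, not better.

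A reader might infer that the plan dilutes the treatment effect. The document does not support that as a general statement. Only the four-visit group main effect is shrunk, section 2.9 does not name it as the test, and the interaction is the more natural choice.

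Finally, the four time levels are listed for the ANOVA, and covariance structure is commonly left to an analysis plan. The absence of a covariance structure is therefore no part of this point. The fixed effects, however, are stated, and baseline adjustment is not among them.

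**Conclusion.** The point holds as an avoidable loss of precision in a stated model, not as a bias or an invalid analysis. At one post visit, adjustment would remove 25% of the variance of a change contrast at the plan's correlation of 0.5, falling to 5% at 0.9. Against raw post values it would remove ρ². The 75% shrinkage is conditional on using the group main effect over all four visits. These sizes rest on equal variances, a common correlation across visits, and the mixed model using the four time levels listed for the ANOVA. The gain at the true correlation is unknown. Apart from the small cost of estimating the baseline slopes, adjustment has essentially no downside.

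**What to change.** In section 2.9, specify one of two forms for QMVIC:
- outcomes at A2, A3 and A4, with fixed effects of group, time, group × time, A1 QMVIC and A1 QMVIC × time; or
- all four visits as outcomes, with the arm means constrained equal at A1.

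Report active-minus-control differences with confidence intervals at each post visit, and do not use a group main effect that averages in A1 as a test of efficacy.

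Apply baseline adjustment likewise to the continuous secondary outcomes. For the Lysholm and ACL-QoL-Sp scores, measured only at A1 and A4, a simple ANCOVA is enough and no baseline × time term applies. The 0–3 effusion grade is ordinal and should not be put through this linear model. If detectable differences are quoted, label α = 0.025 and 15 per arm as assumptions.

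The cost is a change of analysis wording and a few degrees of freedom. No new data are needed. The change should be fixed before any outcome data are seen by arm, since choosing adjustment afterwards would invite criticism.
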